**Fig. 1 Fig1:**
[figure not shown]
Power and sample size according to different intra-class correlations

Since no empirical values are available for the ICC from similar studies with comparable endpoints, we assumed a relatively conservative ICC of 0.2 to determine the sample size. Our assumption resulted in a calculation of 200 older people being needed to achieve the targeted power. Taking into account the dropout rate, which we estimate to be 30% due to the advanced age of the study population, the study requires a sample size of *n* = 260.

The coloured curves show three different estimates of obtained power based on our simulations. Each curve assumed another level of patient-specific autocorrelation. Our assumed target power of 0.8 is highlighted with a horizontal line.

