### Sample size

The sample size calculation was based on the primary endpoint, the BI, for which we model the cumulative probability that the i-th BI Y_it_ will fall into the j-th category or below:

1$$logit\left(P\left({Y}_{it}\le j\right)\right)={\theta}_j-{\delta}_1\left(t{1}_{it}\right)-{\delta}_2\left(t{2}_{it}\right)-u\left({patient}_i\right)$$

i corresponds to the index for observations at time t, j represents the index for categories, {*θ*} is the cut-points, *δ*1 corresponds to the change in BI between PAC entry (baseline) and PAC exit, and δ2 is the change in BI between PAC entry and follow-up measurement at home after 6 months. Patient effects (random effects) are designed as independent and identically normally distributed:

2$$u\left({patient}_i\right)\sim N\left(0,{\sigma}_u^2\right)$$

Of vital importance for the evaluation of the sustainability of PAC is parameter δ2, for which the following hypothesis will be tested:

3$${H}_0:{\delta}_2\le \kern0.5em 0.4,\kern1.5em {H}_1:{\delta}_2>0.4$$

The expected improvement in BI under the alternative hypothesis is >0.4 logits, which corresponds to an odds ratio (OR) of about 1.5. The required sample size to detect an effect under the alternative hypothesis was determined by simulation. We assumed a significance level of α = 0.05 (two-sided test) and a target power of 0.8 (β = 0.2). The obtained power is based on 500 iterative analogue model estimates and was performed for different levels of patient-specific autocorrelation (intra-class correlation [ICC] = 0.1, 0.2, 0.4). As is usual with mixed-effects models, the sample size decreases with increasing ICC (see Fig. 1).

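### The stated 80% power with 200 patients is not delivered by the protocol's own model for the one effect size it names: for a conditional OR of 1.5 tested two-sided against zero, power cannot exceed about 0.65

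*Protocol article*

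**What the plan says.** All of this stands in the protocol article, Methods, Sample size, including the text under Fig. 1.

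- **Model.** Equation 1 is a cumulative-logit model with a patient random intercept: "Patient effects (random effects) are designed as independent and identically normally distributed". The parameter of interest is defined by "δ2 is the change in BI between PAC entry and follow-up measurement at home after 6 months".
- **Hypothesis.** Of this parameter the text says "for which the following hypothesis will be tested". Equation 3 then sets H0: δ2 ≤ 0.4 against H1: δ2 > 0.4.
- **Effect size.** "The expected improvement in BI under the alternative hypothesis is >0.4 logits, which corresponds to an odds ratio (OR) of about 1.5". The Aims and hypothesis section also names an odds ratio of 1.5.
- **Error rates.** Alpha is 0.05 with a two-sided test and the target power is 0.8, evaluated with 500 simulated fits at ICC 0.1, 0.2 and 0.4.
- **Role of the ICC.** "As is usual with mixed-effects models, the sample size decreases with increasing ICC". Then: "we assumed a relatively conservative ICC of 0.2 to determine the sample size".
- **Result.** "Our assumption resulted in a calculation of 200 older people being needed to achieve the targeted power". Allowing for 30% dropout, the target becomes 260.

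The text does not give the value of δ2 used to generate the data, the cut-points, or the definition of the ICC.

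**The concern.** A cumulative-logit model fixes the residual variance at the logistic value. This limits how precisely δ2 can be estimated from 200 patients, and the limit looks too loose for 80% power at 0.4 logits. For the same reason, a larger ICC adds variation between patients without reducing the error within patients. With δ2 held fixed on the conditional scale, the required sample size should therefore not fall as the ICC rises. Finally, if the sample size did fall with the ICC, the cautious value in the grid would be 0.1, not 0.2.

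The power statement is the justification for the size of the trial. If it does not hold for OR 1.5, a non-significant result for δ2 would be read as coming from a study with an 80% chance of detecting that effect when the chance was materially lower.

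**Working it through.** **Inputs from the document.** n = 200; two-sided alpha 0.05; power 0.80; δ2 = 0.4 (or ln 1.5 = 0.405); ICC 0.1, 0.2, 0.4; three BI time points; 30% dropout; 260 enrolled.

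**Assumptions where the document is silent.** The null value is zero. The ICC is on the latent scale, so σu² = ICC/(1 − ICC) × π²/3. δ1 = 0.4. BI is cut into 3, 5, 10 or 21 equally likely categories, with one skewed 5-category case.

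**Step 1. A bound that needs no cut-points or ICC.** A logistic observation carries location information of at most 1/3. Grouping into categories, or not knowing the patient effect, can only lower it. δ2 contrasts two time points, so Var(δ2) ≥ 3/n + 3/n = 6/n.

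- n = 200: SE ≥ √(6/200) = 0.173.
- Power for 0.4: at most Φ(0.4/0.173 − 1.96) = 0.637. For ln 1.5: at most 0.648.
- n for 80% at 0.4: at least 7.85 × 6/0.16 = 294 complete patients.

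**Step 2. Power under equation 1** (information matrix, δ2 = 0.4, n = 200, two-sided 0.05):

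| Categories | ICC 0.1 | ICC 0.2 | ICC 0.4 |
|---|---|---|---|
| 21 | 62.5% | 61.6% | 61.5% |
| 10 | 62.0% | 61.4% | 60.0% |
| 5 | 60.0% | 58.8% | 56.4% |
| 3 | 55.6% | 54.3% | 49.5% |

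The skewed 5-category case gives 56.0% at ICC 0.2. With ln 1.5 instead of 0.4, the ICC 0.2 column rises by about one point (55.4% to 62.7%). Direct simulation with 500 fits gives 59.4/58.6/55.2% (5 categories) and 63.0/59.2/63.6% (10 categories) across the three ICCs. The Monte Carlo error of 500 runs at 80% power is √(0.8 × 0.2/500) = 1.8 points, too small to explain the gap. Power is nearly flat or slightly falling in the ICC.

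At ICC 0.2, 80% power needs about 300 to 330 complete patients with 5 to 21 categories, and up to 367 with 3.

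**Step 3. Readings that might recover 80% at n = 200 and ICC 0.2.**

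- One-sided 0.05 alone: 66% to 74%.
- Marginal-scale effect alone, two-sided: 0.4 × √(1/(1 − 0.2)) = 0.447 on the conditional scale, giving 64% to 71%.
- Both together: about 81% with 10 or 21 categories. With 10 categories this reading gives 77.2/80.8/88.7% across the ICCs, so the required n does fall with the ICC.
- A larger generating effect: with SE 0.1775 (21 categories), 2.80 × 0.1775 = 0.497, OR 1.64; with SE 0.1934 (3 categories), 2.80 × 0.1934 = 0.542, OR 1.72.
- The printed null δ2 ≤ 0.4: power at δ2 = 0.4 is no more than alpha. For 80% power against that null, δ2 would have to be at least 0.4 + 2.80 × 0.173 = 0.884, an OR of about 2.4.

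**Step 4. With 260 enrolled and 30% lost at T3.** 260 × 0.7 = 182 patients have T3 data. Using completers only, power for ln 1.5 at ICC 0.2 is 52% to 59%. Keeping the dropouts' baseline data, a simulation with 10 categories and δ2 = 0.4 gave 0.617 (SE 0.175). The OR detectable with 80% power is exp(2.80 × 0.175) = 1.63 in that case. For completers with 5 categories, the SE is 0.1832 × √(200/182) = 0.192 and the OR is exp(2.80 × 0.192) = 1.71.

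**The case against.** The decisive input is missing from the document. The generating δ2 is described only as above 0.4, and a value near 0.5 logits satisfies that and reaches roughly 80%. One coherent reading, a marginal effect with a one-sided test, reproduces both the 200 and the stated direction of the ICC effect, and equation 3 is one-sided in form. Fig. 1 is not available here. The article says relatively conservative, not most conservative, and the choice between 0.1 and 0.2 hardly moves the power in Step 2. The study is also an uncontrolled exploratory pilot.

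Much of this stands. A reader might infer that the true power is about 60%, that testing 0.4 against zero is the most favourable reading, or that the simulation was computed wrongly. The documents do not support any of these, because they do not say which effect, scale or null the simulation used. The fault may lie in the reporting rather than the calculation. The ICC wording has little numerical consequence.

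What does not stand is the 80% as reported. The marginal, one-sided reading contradicts the stated two-sided test and the conditional effect in equation 1. No generating effect above OR 1.5 is given anywhere. The exploratory label does not remove the need for a stated alpha, power and effect size to agree.

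**Conclusion.** The point holds in a limited form. For the only effect size the article names, taken as conditional on the patient as in equation 1 and tested two-sided at 0.05 against zero, 200 patients cannot give more than about 0.64 to 0.65 power. That ceiling depends on neither the cut-points nor the ICC. The range of about 0.54 to 0.63 at ICC 0.2 does rest on the assumed categories and the latent-scale ICC.

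Under the null as printed, the power at 0.4 is at most alpha, so equation 3 and the power calculation cannot both stand as written. The statement that the sample size falls with the ICC does not hold for a fixed conditional δ2. Calling 0.2 conservative sits badly with the article's own direction, under which 0.1 is the cautious value; this is a minor matter. The step from 200 to 260 is a separate question and is not counted here.

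**What to change.** 1. Reconcile equation 3 with the power calculation, and state the null value and the sidedness of the test.
2. State the generating δ2 and its scale (conditional or marginal), the ICC definition and the BI cut-points.
3. Rerun the simulation with these inputs and the planned 30% loss at T3. Then report either the power for OR 1.5 or the OR detectable with 80% power with 260 enrolled. If the test is two-sided against zero, expect a power of about 0.5 to 0.65, depending on the categories and on whether dropouts' baseline data are used, or a detectable OR of about 1.6 to 1.7.
4. Remove the word conservative and the statement that the sample size decreases with the ICC, unless the effect is defined on a scale where it does.

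The cost is a few hours of simulation and a less favourable power statement. No change in enrolment is needed.

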### Study design and setting

The Prevention Admission into Nursing homes (PAN) study is a three-site, multicentre, exploratory, prospective, longitudinal pilot study in Swiss nursing homes without a control group. All centres (*n* = 3) are located in Zurich and the study will examine older people (*n* = 260) enrolled in PAC treatment. Additionally, a qualitative process evaluation will assess relatives’ perspectives (*n* = 30).

This study will be led by Zurich University of Applied Science’s health department and the department of Nursing Homes of the City of Zurich (PZZ) and will last approximately 24 months.

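### The 30% dropout allowance is added to 200 rather than divided out, so 260 enrolled leaves 182 expected 6-month Barthel values, not 200; the stated derivation needs restating, though no power loss is shown

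*Protocol article*

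**What the plan says.** The Sample size section of the protocol article bases the calculation on a cumulative-logit mixed model for the Barthel Index, with a random effect for each patient. The parameter that carries the sustainability question is defined there: "δ2 is the change in BI between PAC entry and follow-up measurement at home after 6 months". The design values are given as "We assumed a significance level of α = 0.05 (two-sided test) and a target power of 0.8 (β = 0.2"), and power was found by simulation.

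The text under Fig. 1 then gives the numbers. For the intra-class correlation, "we assumed a relatively conservative ICC of 0.2 to determine the sample size". The result is "Our assumption resulted in a calculation of 200 older people being needed to achieve the targeted power". Dropout is the next step, at a rate "which we estimate to be 30% due to the advanced age of the study population, the study requires a sample size of" 260.

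The section Study design and setting confirms that this is the number entering the study, not the number left at the end: "the study will examine older people (*n* = 260) enrolled in PAC treatment". The Abstract gives the same figure.

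**The concern.** An allowance for dropout should make the number left after the loss equal to the number required. That means dividing by the retained fraction. Adding the dropout percentage to the requirement gives too small a number, and the gap grows with the dropout rate. At 30% it is no longer a rounding matter.

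The loss also falls where it counts. The key parameter contrasts PAC entry (T0) with the measurement 6 months after discharge (T3), which is the last visit. If the derivation is wrong, two things are at stake: the number of 6-month values the study can expect, and whether the 80% power attached to 200 patients carries over to the 260 that the article announces.

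**Working it through.** **Inputs, all from the Sample size section:** requirement before dropout 200; dropout 30%; stated total 260; two-sided α 0.05; target power 0.80; ICC 0.2, with 0.1 and 0.4 also simulated. The 200 is taken as stated, because the article does not give the cut-points and effect size needed to rebuild the simulation.

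**1. Reproducing the stated figure.** 200 × (1 + 0.30) = 260, an exact match. The article prints no formula, so the multiplication is inferred. The next step does not depend on it.

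**2. What 260 delivers.**
- 260 × 0.70 = 182 patients expected at T3
- 200 − 182 = 18 short (18 / 200 = 9%)
- Loss at which 200 remain: 1 − 200/260 = 23.1%
- Enrolment implied by 200 completers and 30% loss: 200 / 0.70 = 285.7, so 286 (286 × 0.70 = 200.2)

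**3. Power if only completers were analysed.** Assume exactly 80% power at 200 and a standard error proportional to 1/√n. The standardised effect at 200 is 1.960 + 0.842 = 2.802. At 182 it is 2.802 × √(182/200) = 2.673, and Φ(2.673 − 1.960) = 0.762, about 76%.

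**4. Power for the kind of model planned.** A mixed model keeps the earlier values of patients lost before T3. A linear random-intercept model with total variance 1 and intra-class correlation ρ serves as an approximation, with T3 missing at random in 78 of 260 patients.

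- 200 complete patients: Var(δ2) = 2(1 − ρ)/200. At ρ = 0.2 this is 0.00800.
- Dropouts keep T0 and T1: with b = ρ/(1 + ρ), Var(δ2) = [1 − 2ρ²/(1 + ρ)]/182 + [(1 − b)² + b² − 2b(1 − b)ρ]/260. At ρ = 0.2, b = 1/6, which gives 0.9333/182 + 0.6667/260 = 0.00513 + 0.00256 = 0.00769.
- Dropouts keep T0 only: Var(δ2) = (1 − ρ²)/182 + (1 − ρ)²/260. At ρ = 0.2 this is 0.96/182 + 0.64/260 = 0.00527 + 0.00246 = 0.00774.

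The equivalent number of complete patients is 200 × Var(200 complete)/Var(260 with loss). Power is Φ(2.802 × √(equivalent/200) − 1.960).

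| ICC | Dropouts keep | Equivalent complete patients | Power |
|---|---|---|---|
| 0.1 | T0 and T1 | 210.7 | 82.0% |
| 0.1 | T0 only | 210.4 | 82.0% |
| 0.2 | T0 and T1 | 208.0 | 81.5% |
| 0.2 | T0 only | 206.8 | 81.3% |
| 0.4 | T0 and T1 | 203.8 | 80.7% |
| 0.4 | T0 only | 200.0 | 80.0% |

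**5. Cross-check by simulation.** Simulated standard errors of δ2 were 0.187 with 182 complete patients, 0.178 with 200 complete, and 0.175 with 260 enrolled and 30% of T3 missing completely at random. The last two give 2.802 × 0.178/0.175 = 2.850 and Φ(2.850 − 1.960) = 0.81, in line with the table.

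**The case against.** The strongest reply is that the arithmetic slip does no harm. The Statistical analysis section applies the same mixed model to the primary endpoint, and nothing in the article restricts the analysis to patients with a 6-month value. Partial data then make up the shortfall, and in the approximation above power does not fall below 80% at any of the three ICC values. The 200 is itself soft: with 500 simulation runs the Monte Carlo standard error near 80% power is √(0.8 × 0.2/500) = 1.8 percentage points, and the ICC is an assumption made without empirical values. The study is also a single-arm exploratory pilot.

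Most of this stands. A reader might infer from 182 against 200 that the trial is underpowered at 76%, or that it must recruit 286. The documents support neither. The 76% belongs to a completers-only analysis that the article does not plan, and it also assumes exactly 80% power at 200. Dividing by 0.7 would not settle a problem of non-random loss either, because that is a matter of bias, which a larger sample does not remove.

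The reply does not rescue the sentence as printed. The article presents 260 as 200 adjusted for 30% dropout. It does not appeal to partial data, and the simulation it describes varied the ICC with no mention of missing T3 values. That 260 performs adequately under random loss is a coincidence the article neither claims nor shows. The recovery rests on loss at random, in a study where dropout is attributed to advanced age and the last measurement is made at home. At ICC 0.4 with only the entry value kept, the margin is nil.

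**Conclusion.** The stated sample size does not follow from its own inputs. With 30% dropout, 260 enrolled gives 182 expected 6-month Barthel values, 18 (9%) below the 200 the article says are needed, and the figure tolerates a loss of about 23%. This part rests only on the article's printed numbers.

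The effect on power is a separate matter and is not adverse on the evidence available. If loss is at random and the mixed model uses all available values, power is about 80% to 82% across ICC 0.1 to 0.4. That range rests on a linear approximation to the ordinal model and on exactly 80% power at 200 complete patients. What has to be corrected is the derivation and the expected number of completers. The 80% power should be shown for the design as it will run, rather than carried over from 200 complete patients.

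**What to change.** Keep 260 and correct the account of it in the Sample size section:

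- State that 260 enrolled gives 182 patients expected at T3 under 30% loss, and that 200 would remain only with a loss of at most 23%.
- Rerun the existing power simulation with 260 enrolled and 30% of T3 values missing, and report the resulting power in place of the figure for 200 complete patients.
- Say that this power assumes loss at random and that the mixed model uses the T0 and T1 values of patients lost before T3.
- If 286 is mentioned, cite it only as the enrolment implied by 200 completers and 30% loss, not as a recruitment requirement.

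The cost is a few corrected sentences and one rerun of a simulation that already exists. No extra patients are needed. By the approximation above, the reported power need not be lower than the present target.

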### Participants

The study population will consist of older people enrolled in a PAC treatment programme and their informal caregiver network.Older people

The following inclusion criteria will be applied to the older people: must be ≥65 years old; admitted to one of the nursing homes and participating in the running PAC programme; assessed with a PAC potential ≥3 (see Fig. 2) and conditions impairing physical functioning; able to communicate in German; and must have provided informed consent.

**Fig. 2 Fig2:**
[figure not shown]
Recruitment process for post-acute care admission

2.Informal caregiver network

The following inclusion criteria will be applied to the informal caregiver network (i.e., primary relatives in charge or trusted persons): must have the capacity and the capability to provide informed consent; be able to communicate in German; and be of legal age.

For a description of the recruitment, refer to Fig. 2. The department of Nursing Homes of the City of Zurich (PZZ), namely the third author, will be in charge and administrate the study participants’ enrolment.

### Intervention

Typically, patients are selected for geriatric rehabilitation during their acute hospital stay (i.e., usual rehabilitation care). PAC provides a differentiated geriatric assessment and estimates the PAC potential for those affected by musculoskeletal diseases, injuries and circulatory diseases. PAC provides rehabilitation for older people who leave an acute hospital and are not sufficiently independent to resume living at home or can no longer cope at home. The aim is to help them reach the point at which they can reintegrate into their homes. Interprofessional teams conduct PAC programmes in nursing homes (see Fig. 2). Unfortunately, no uniform international definition of PAC exists [5]. Wang and colleagues (2019) proposed a clinical perspective with five goals: 1) the potential to live independently, 2) a comprehensive assessment, 3) enhancing patients independent living, 4) program duration 6 weeks, and 5) individual assessment mechanisms [5]. PAC treatment and plans with individual goals are developed according to the comprehensive assessment of cognition, nutritional status, physical function and mobility and basic activities of daily living [22]. Nursing, medical and therapeutic interventions and treatments support those affected in regaining the greatest possible independence. PAC gives older people more time than in a traditional rehabilitation setting to take on as much as possible by themselves and thus strengthen their self-care abilities.

Treatments with a rehabilitative approach are characterised by close interprofessional cooperation focusing on functional activities, education and psycho-social support [37]. Physicians are primarily responsible for PAC assessment, drug treatment, follow-up and evaluation. Therapeutic specialists, such as physiotherapists and occupational and speech therapists, are tasked with improving functioning, and nurses transfer and integrate (re)gained functions into the daily lives of older people. For example, the handgrip strength regained through targeted physiotherapy is transferred to everyday life through targeted nursing interventions. Patients are given sufficient time and individual support to select, prepare and eat their bread rolls for breakfast independently instead of simply feeding them. Overall, providing advice, particularly on mobility and self-care, to patients and their caregivers is an essential nursing intervention in PAC [37]. Social service providers carefully plan the return home and subsequent outpatient care. Furthermore, they initiate necessary measures in collaboration with the primary relatives.

A PAC programme lasts an average of 8 weeks and a maximum of 10 weeks based on the PAC potential assessment. If, after this time span, a return home is not possible, even with appropriate support, suitable alternatives are explored together with the affected person. In cases where a return home is likely after an extended stay, the older person is transferred to a specialised nursing ward to attain adequate independence and functioning.

### Endpoints

The following outcomes will guide the evaluation of the PAC programme.Functional status as the primary endpoint

Functional status will be measured with the BI [38] at PAC entry (T0), PAC exit (T1) and 6 months after PAC discharge to the home environment (T3). The BI is a ten-item scale with either 0, 5, 10 or 15 points allocated for each item (maximum total score of 100 points = maximum functional status). The BI is a validated and common instrument used to assess functionality in rehabilitation care [38, 39]. For use with older and multi-diagnosed people, there might be imprecision when testing takes place by different observers [40]. To the best of our knowledge, little is known about the sensitivity to changes in the BI [41]. A clinically meaningful change is to be determined by the patients themselves. Recommended BI cut-off points to determine overall independence are problematic. Overall, a five-point difference can have completely different meanings for individual daily life independence. Collin and colleagues [39, 41] recommended that a 20-point change be considered as clinically significant. For the individual use of BI, other endpoints must also be considered.

All items will be collected through direct observation by study personnel or interviews with those affected, their relatives or the nursing staff.2.Independence as the secondary endpoint

Independence will be measured via the informal network and the following nine criteria: delirium, cognition, mobility, falling concerns, frailty, body mass index (BMI), PAC capability and quality of life. The details of each criterion are as follows:Delirium: The assessment of delirium will be performed with the Delirium Observational Scale (DOS) at PAC entry (T0) [42]. The instrument has shown a high internal consistency with a reported Cronbach’s alpha = 0.96 and is considered valid and reliable for the early detection of delirium in older people [37, 38]. Delirium per shift will be evaluated using 13 items and four levels (never, sometimes, always or do not know). The occurrence of more than three criteria indicates a positive delirium screening and will trigger additional assessment.Cognition: The degree of cognitive performance will be measured using the Mini-Mental State Examination (MMSE) at admission (T0) and at home (T3) [43]. The reliability of the MMSE has been reported with a reported Cronbach’s alpha = 0.91 [44]. The sum of the MMSE spans from zero to 30 points, with 30 being the optimal result. Cognitive impairment is diagnosed at an MMSE sum of less than 24 points [43, 45, 46].Mobility: Mobility will be measured using the Short Physical Performance Battery (SPPB) at PAC entry and 6 months after release from the PAC to the home environment (T0, T3) [47]. SPPB has proven reliable with a Cronbach’s alpha = 0.87 [48]. The SPPB includes balance, a four-metre walking test and the stand-up test. A score of 10–12 points represents normal mobility, a score of 7–9 points indicates an increased risk of gait disorder and a score of less than 6 points indicates a very high risk of increasing gait disorder and loss of independence [47].Falling concerns: Concerns regarding falls will be measured with the German version of the Falls Efficacy Scale-International (FES-I) at PAC entry and 6 months after release from the PAC to the home environment (T0, T3). The German version of the FES-I has a high internal consistency (Cronbach’s α = 0.96) and retest-reliability (*r* = 0.96) [49]. The FES-I questionnaire consists of 16 items in which concerns about different activities and cases are raised. The answers are graded as follows: one = no concerns; two = some concerns; three = moderate concerns; and four = very great concerns. A minimum score of 16 indicates no concerns about falling, and a maximum score of 64 indicates severe concern about falling [49, 50].Frailty: Frailty will be assessed using the frailty screening questionnaire [51, 52] at PAC entry and 6 months after release from PAC to the home environment (T0, T3). The questionnaire has been shown to be a valid and reliable instrument with a test-retest reliability total score of *r* = 0.937 [53]. The frailty screening questionnaire examines five factors (weight loss, fatigue, walking speed, physical weakness and activity level). The assessment is “met” or “not met”, with zero factors met indicating robustness, one to two factors met indicating a pre-frail status and less than three factors met indicating frailty [51, 52].Weight/height/BMI: Weight, height and BMI measures will be used as co-variates of frailty [8, 54]. All three elements will be measured at entry and 6 months after release from PAC to the home environment (T0, T3) [8].PAC capability: PAC capability assessment will be conducted using the Resident Assessment Instrument for Nursing Homes (RAI_NH) to determine the degree of care dependency at PAC entry (T0) and at PAC discharge (T1). The “Minimum Data Set” category of the Swiss RAI_NH is a needs assessment tool [55]. The RAI_NH care dependency score ranges from tier 1 (lowest) to 12 (highest) [55]. All items will be collected through direct observation or interviews with those affected, their relatives or the nursing staff.Quality of life: Quality of life will be measured as a subjective screening of health status on a numeric rating scale ranging from “excellent (10)” to “poor (0)” as an influence on functionality. It will be measured at entry, discharge and 6 months after release from the PAC to the home environment (T0, T1 and T3).Informal network: The frequency of use of formal and informal caregiver networks to secure the home environment will be measured by interviewing the primary relative in charge. The frequency of informal network use will be measured 6 months after discharge from PAC to the home environment (T3).

Data from the study participants will be routinely collected four times (see Table 1). Socio-demographic data of the participants will also be collected, particularly to analyse sex-specific aspects.

**Table 1 Tab1:** Outcome Measurements during the Intervention Schedule

Timepoint	T0	T1	T2	T3
	PAC admission	PAC discharge	3 months after discharge	6 months after discharge
